### Participant recruitment and randomization

Following procedures we have used in our earlier studies, media announcements (newspapers, radio, and websites) will be used to recruit individuals concerned about their gambling and interested in web-based self-directed treatment. Inclusion criteria will be identical to Hodgins et al. (2009): 18 years of age or older; perception of a gambling problem and scoring a 3 or greater on the Problem Gambling Severity Index of the Canadian Problem Gambling Index (PGSI- CPGI; [44]); gambled at least once in the past month; not involved in treatment at present (includes Gamblers Anonymous and any medical or psychological treatment where gambling problems are addressed); willingness and ability to access a website in English (to ensure reading ability); willingness to have telephone contacts recorded, willing to provide follow-up data on gambling; willingness to provide the name of a collateral (family or friend) to help locate them for follow-up interviews and the name of the same or a different collateral for data validation. Use of psychiatric medications for other mental health disorders will not be an exclusion criterion, although use will be assessed and monitored as a potential treatment moderator.

To ensure an adequate number of participants are assessed within the timeframe, recruitment will occur across Canada. Both urban and rural settings will be targeted. Interested individuals will be provided with a website address with information about the study, including eligibility criteria and a toll-free number to call or email address to use if interested. Having participants access a website at this point in the recruitment process is designed to minimize the number of participants who are randomly assigned but never access the intervention or control website (30% in one of our recent alcohol trials).

Individuals will be contacted by telephone and if they meet eligibility criteria and provide informed consent, they will receive a brief telephone assessment (gambling history and behaviour, self-efficacy) and then will be randomly assigned to one of the two intervention conditions, stratified on sex, gambling problem severity and treatment history (yes or no) [45] using MINIM, a computer program which uses the method of minimization. Problem severity, based on the NODS described below, will be defined as low-moderate (6 or fewer DSM-IV criteria) or high (7–10 criteria).

### Intervention conditions

#### Self-change Tools (SCTs)

SCTs, as described above, integrate the self-directed written materials [24] that were evaluated in the three brief treatment trials [13,15,46] and a trial of a self-directed relapse prevention for gambling problems [47]. A major focus is to provide individuals with clear and concise behavioural and cognitive strategies for meeting the goal of reducing or quitting gambling. The materials are presented as a series of options from which participants will choose what strategies seem most relevant to them. Participants will have ongoing access to the site over the follow-up period to make it as similar as possible to other web resources in terms of accessibility. The enhancements to the workbook content include three features. First, whereas the workbook encourages individuals to self-monitor their gambling, the website will provide a more structured option for individuals to maintain an online log of gambling and gambling urges. A further option will be to use a smartphone application to collect this self-monitoring information. A second enhancement is the expansion of the self-assessment component of the workbook to include more structured personalized normative feedback of gambling involvement. Again, the workbook provides some of this feedback but in a less comprehensive way. The third enhancement is the option for individuals to receive motivational email or text reminders of their progress and goals. This feature is somewhat similar to the motivational telephone booster calls provided in Hodgins et al. (2009).

#### Check your gambling (CYG; http://www.CheckYourGambling.net)

CYG will be used as the control intervention. Although we hypothesize that the SCTs will be a more powerful intervention than the CYG, CYG is a credible and ethically appropriate control comparison. In the CYG, the participant completes a brief assessment and then receives a personalized feedback report. The personalized feedback materials start out with a brief statement of the purpose of the report (“help to give you a picture of your gambling and let you know how your gambling compares with other Canadians”). The person is then provided with a summary of the types of gambling engaged in, along with a comparison of how this relates to other Canadians of their sex, a summary of their Problem Gambling Severity Index score and interpretation and a description of the types of gambling cognitions that the person endorsed. The final element of the feedback is a list of techniques that the person could adopt to lower the risk associated with their gambling.

### Baseline assessment

The brief telephone baseline assessment (adapted from Hodgins et al. 2009) will include a demographic profile (age, sex, education, marital status, income, ethnicity and racial status, employment status) and a gambling, mental health and treatment history including a timeline interview of types of gambling (online, land-based), frequency, and money spent for the past three months [48,49]. Problem gambling severity will be assessed using the past year Problem Gambling Severity Index and the lifetime and past three month version of the NORC DSM-IV Screen for Gambling Problems (NODS) [50,51] which indicates DSM-IV severity. Hodgins [52] administered the NODS to problem gamblers as part of a 1-year follow-up after a brief treatment to assess its utility as a treatment outcome measure. Internal reliability was fair to good and the factor structure and item-total correlations supported the existence of a single higher order construct that correlated moderately with gambling behavior and outcome. Self-efficacy will be administered using the Gambling Abstinence Self-efficacy Scale (GASS, [53], a 21 item self-report scale with evidence of concurrent and predictive validity in problem gambling treatment samples. In addition, participants will be asked to identify a treatment goal (quit or reduce gambling) and how successful they think they would be (0 “not at all” to 10 “extremely”) in the next 6 months and in the next 12 months. The Kessler 10 (K10) questionnaire will be included to provide a continuous measure of general psychological distress that is responsive to change over time. The K10 has been well validated and its brevity and simple response format are attractive features. It also produces a summary measure indicating probability of currently experiencing an anxiety or depressive disorder [54,55]. Quality of life will be assessed by the WHOQoL-8, an eight item version of a widely used measure. This short form has been used in a number of countries, is robust psychometrically, and overall performance is strongly correlated with scores from the original WHOQoL [56].

### Follow-up assessment

After three, six and twelve months, a follow-up assessment of gambling behaviour (timeline method), problem gambling severity (NODS), self-rated improvement, self-efficacy (GASS), psychiatric distress, quality of life, use of other treatment resources, and impressions of site features and tools will be conducted. Although it would appear efficient to conduct follow-up assessments via the Internet, previous experience has shown that attrition is extremely high with this type of design. In our previous research, follow-up interviews were conducted via telephone with good follow-up rates. As a result, our follow-up interviews in this study will be conducted via telephone. We will collect extensive contact information for participants to minimize losing contact (e.g., contact information for family and friends, work contact, email contact, etc.).

Participants will also be asked to provide the name of a collateral (family or friend) who can confirm their self-reported gambling behaviour through a brief telephone call. In Hodgins et al., (2001, 2009) agreement between participants and collaterals was r = .61 and ICC = .69 for dollars lost and r = .66 and ICC = .53 for days of gambling, indicating fair agreement. As in previous research [49,57], collaterals who described themselves as more confident showed better agreement and in general collaterals tended to report less gambling than participants suggesting that participant reports are not attenuated by minimization.

### Process measures

We will have access to a complete record of the amount and type of use participants make of the SCTs (and the CYG). Following methods used by Danaher (2008) and Strecher (2008), we will operationalize degree of involvement with SCTs by recording the number of times the participant accesses the site as well as the number of tools the participant uses (as assessed by page views, form completions, etc.) and length of involvement with the site (e.g. use of the site over time). This information will be used to test the mediation hypothesis that degree of involvement is related to success at overcoming gambling problems.

### Primary and secondary outcome variables

Two major outcome variables for testing the primary and secondary hypotheses will be: mean days per month gambling and NODS scores. Mean dollars lost per gambling day, total dollars lost and self-rated improvement will be used as secondary outcome variables. Days and dollars spent gambling will be calculated for the three months pre-treatment and for each follow-up period. The data will be inspected for approximate normality or symmetry and, if necessary, subjected to appropriate transformation.

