### Analyses plan

Primary analyses for Hypothesis 1, comparing outcomes for the two groups, will be based on the appropriate random effects model to properly account for the longitudinal nature of this data. Condition (2) and Time (0,3,6,12) will be modeled as fixed factors while the participants will be modeled as random factors. Separate analyses will be conducted for each primary and secondary outcome variable. This same analytic approach will be used for Hypothesis 2 and 3, examining moderators. Baseline self-efficacy, past use of treatment, and baseline NODS scores will be included as additional factors. For Hypothesis 3 and 4, the mediation hypotheses, the procedures recommended by Preacher and Hayes [58] will be conducted using a series of random effect models. Missing data should not be a major issue but techniques for these matters may be used depending on the nature, location and type of missingness.

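### Dollars lost per gambling day has no value for participants who quit, so it compares only those still gambling; total dollars lost may also mix periods of unequal length

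*Protocol article*

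**What the plan says.** Under Primary and secondary outcome variables, the major outcomes are "mean days per month gambling and NODS scores". For the rest: "Mean dollars lost per gambling day, total dollars lost and self-rated improvement will be used as secondary outcome variables". The same section gives the windows: "Days and dollars spent gambling will be calculated for the three months pre-treatment and for each follow-up period". The only data handling it mentions is a transformation towards normality or symmetry where needed.

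Quitting is an intended result. The SCT section describes "behavioural and cognitive strategies for meeting the goal of reducing or quitting gambling", and at baseline "participants will be asked to identify a treatment goal (quit or reduce gambling"). Entry requires that the person "gambled at least once in the past month".

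On timing, the Follow-up assessment section has: "After three, six and twelve months, a follow-up assessment of gambling behaviour (timeline method"). On analysis, the Analyses plan has: "Condition (2) and Time (0,3,6,12) will be modeled as fixed factors while the participants will be modeled as random factors", with a separate analysis for each primary and secondary outcome. Missing data are not expected to be a major issue there, and no method is fixed.

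**The concern.** Dollars per gambling day is a ratio whose denominator the intervention is meant to lower, to zero for anyone who quits. Every participant has a value at baseline, because recent gambling is an entry condition. Afterwards the value disappears for exactly those who reached the quit goal. What remains at follow-up is a comparison of continuing gamblers, no longer of the groups as randomised. If the intervention makes more people quit, and lighter spenders are the likelier quitters, the SCT arm can look neutral or worse on this outcome because it works.

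The second, smaller matter is scale. Days are expressed per month and total dollars is not. If the follow-up periods differ in length, totals at different visits are not comparable, yet they enter one model over Time 0, 3, 6 and 12.

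**Working it through.** **1. The plan's own figure.** It concerns days and NODS, not dollars, and serves here only for the number followed. Inputs from Sample size and power analysis: α = 0.025 (taken as two-sided), power 0.80, correlation 0.5, attrition 15%, and a medium effect (d = 0.5 assumed, as no SD is given). The change-score SD is √(2(1 − 0.5)) = 1. Then n per arm = 2(2.241 + 0.842)²/0.5² = 76.04, so 77 per arm and 154 in total; 154/0.85 = 181.2, so 182 enrolled. The article has about 153 and 180, so the figure reproduces. Followed: 180 × 0.85 = 153, or 76.5 per arm.

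**2. How many have a value.** At zero days the outcome is 0/0. With abstinence share q in a period, 76.5 × (1 − q) per arm have one. The article gives no q, so these are assumptions (SCT/CYG):
- 10%/10%: about 69 and 69
- 20%/10%: about 61 and 69
- 30%/20%: about 54 and 61
- 40%/20%: about 46 and 61

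**3. Direction of the selection effect.** Large simulation. Assumed: log-normal dollars per day (log-mean 5, log-SD 1), latent correlation −0.5 between log spend and quitting, and no effect of SCT on spend per day. Ratios are SCT/CYG from unrounded means.

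| Abstinent SCT/CYG | Continuing gamblers only | Ratio | Abstainers counted as 0 | Ratio |
|---|---|---|---|---|
| 20%/10% | 278 / 262 | 1.063 | 223 / 236 | 0.945 |
| 30%/15% | 296 / 270 | 1.097 | 207 / 229 | 0.903 |
| 40%/20% | 316 / 278 | 1.135 | 189 / 223 | 0.851 |

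The order of the arms reverses once abstainers count.

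**4. Size at about the trial's scale.** Simulation with 90 per arm, log-normal spend (SD 1.0 between persons, 0.5 within), logistic quitting with slope 0.5 to 1.5 on log spend, quit rates 20% against 35% or 40%, and no true effect on dollars per day.
- Plain comparison of non-quitters: spurious SCT excess of roughly 8-23%.
- With baseline used, as in the planned model: about 2-5%, test size about 5-8% at nominal 5%.
- With baseline used, but quitting driven by current rather than usual spend: up to about 11%, test size up to about 13%.
- Equal quit rates with the same selection in both arms: no bias.

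Baseline helps because it carries much of the information on who was a light spender. It does not change the question: the model in effect asks what abstainers would have lost per day had they gambled.

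**5. Total dollars.** Take the follow-up periods as the intervals between visits: 3, 3 and 6 months, after a 3-month baseline.
- A constant loss R per month gives 3R, 3R, 3R, 6R. For R = 500: 1500, 1500, 1500, 3000.
- A true halving in the last period gives 6 × 0.5R = 3R, the same as baseline.
- A constant arm difference of 200 per month appears as 600, 600, 1200. One that fades from 200 to 100 in the last period appears as 600, 600, 600, as if sustained.
- With correlation ρ between a person's monthly losses, the variance ratio of a 6-month to a 3-month total is 6(1 + 5ρ)/[3(1 + 2ρ)] = 2(1 + 5ρ)/(1 + 2ρ): 2 at ρ = 0, 3.5 at ρ = 0.5, 4 at ρ = 1.

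**The case against.** **On dollars per gambling day.** Abstainers are not lost from the trial: both primary outcomes and total dollars are defined for them, and one of three secondary outcomes is affected. The article states no exclusion of abstainers; a zero-day rule could stand in an analysis plan that is not shown. The quit rates are assumed, and a gap of 15 to 20 points against a credible active control may be generous. A reader might also take the 8-23% as the bias of the planned analysis. That does not follow: it belongs to a plain comparison at follow-up, whereas the planned model includes Time 0 and leaves a few percent in most of these settings. All of this stands as a limit on size. It does not supply a value where the denominator is zero, and neither does a transformation.

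**On total dollars.** A reader might infer that the windows are 3, 3 and 6 months as a matter of fact. The article never states the follow-up look-back. That reading is the natural one, but a fixed three-month look-back at each visit would remove the problem. A reader might also infer that the 12-month treatment comparison is biased, or that its variance is four times as large. Neither is supported. Both arms share the same window at a visit, and a doubling common to both goes into the Time effect. After a log transformation the doubling is an additive constant that Time absorbs, apart from the handling of zeros. The variance ratio lies between 2 and 4, and 4 needs perfectly correlated months.

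**Conclusion.** The point holds for dollars per gambling day as the article fixes it. The outcome does not exist for people who meet one of the two treatment goals, so its tested comparison rests on a group selected after randomisation and cannot credit abstinence. This follows from the definition and needs no assumption. The amount of distortion does: it is likely a few percent under the planned model, up to about 11% in a less favourable setting, and absent if quit rates and selection are the same in both arms.

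For total dollars the point is conditional on the periods being the intervals between visits. In that case the raw time profile, and any effect pooled over visits, are distorted; the arm comparison at a single visit is not. Nothing here touches days per month or NODS. It is worth correcting before analysis, as a matter of secondary outcomes.

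**What to change.** - Define the dollar outcome as mean dollars lost per month in the period, or use the same three-month window at every visit, and state the look-back.
- Enter zero for participants who did not gamble in the period, and analyse all randomised participants with follow-up.
- Keep dollars per gambling day only as a descriptive measure among those still gambling, shown beside the proportion abstinent by arm at each visit.

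The cost is small. Dollars per gambling day loses its status as a tested outcome. The timeline interviews already supply everything needed, so no new data are required, and the primary outcomes and sample size stay as they are.

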### Blinding

Participants will be aware that they will be assigned to one of two intervention options, although neither one will be described as potentially superior. Baseline assessment occurs prior to randomization. Follow-up assessments are conducted by interviewers who will be blind to participant assignment.

### Analyses plan

Primary analyses for Hypothesis 1, comparing outcomes for the two groups, will be based on the appropriate random effects model to properly account for the longitudinal nature of this data. Condition (2) and Time (0,3,6,12) will be modeled as fixed factors while the participants will be modeled as random factors. Separate analyses will be conducted for each primary and secondary outcome variable. This same analytic approach will be used for Hypothesis 2 and 3, examining moderators. Baseline self-efficacy, past use of treatment, and baseline NODS scores will be included as additional factors. For Hypothesis 3 and 4, the mediation hypotheses, the procedures recommended by Preacher and Hayes [58] will be conducted using a series of random effect models. Missing data should not be a major issue but techniques for these matters may be used depending on the nature, location and type of missingness.

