### Sample size and power analysis

We propose to collect a sample of 180 participants and we estimate (based upon Hodgins et al., 2009) that we will successfully follow about 153 participants at three months. This number will ensure a heterogeneous sample of individuals that will provide a valid assessment of the perceived value of different components of the SCTs. Based upon previous experience, about half will be of each sex. This number will also provide sufficient power to conduct the proposed statistical tests comparing the two conditions, based upon gambling frequency and NODS data from Hodgins et al. (2001, 2009), assuming a correlation of .5 between baseline and follow-up values, power = 0.80 and a Bonferroni corrected α = .025 (.05/2 outcome variables). This sample size is estimated so as to be sufficient to detect a difference of about 2 gambling days per month between conditions at each follow-up interval (medium effect size). This degree of difference is clinically meaningful in terms of gambling involvement. Similarly, this sample size will detect a 1 point difference on the NODS at 12 months. Given the complexity of estimating power for HLM models, these calculations are based upon a more simple repeated measures ANOVA model [59], with an attrition rate (i.e., not followed after baseline assessment) estimated to be 15%. The proposed hlm analysis will likely have greater statistical power because all observed data are included.

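### The model for Hypothesis 1 carries baseline as a Time level and states no baseline adjustment; a baseline-adjusted follow-up contrast would gain power at no cost beyond wording

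*Protocol article*

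**What the plan says.** The Analyses plan section of the Protocol article describes a random effects model for Hypothesis 1: "Condition (2) and Time (0,3,6,12) will be modeled as fixed factors while the participants will be modeled as random factors". It names no Condition x Time term, contrast or time point. It calls for a separate analysis of every primary and secondary outcome, and for the same approach to the moderator hypotheses (2 and 3). Directly after the moderators it adds: "Baseline self-efficacy, past use of treatment, and baseline NODS scores will be included as additional factors". The Blinding section places the baseline assessment before randomisation.

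The Sample size and power analysis section works from a repeated measures ANOVA, "assuming a correlation of .5 between baseline and follow-up values", with "power = 0.80 and a Bonferroni corrected α = .025 (.05/2 outcome variables". Its target for gambling frequency is "a difference of about 2 gambling days per month between conditions at each follow-up interval (medium effect size". For the second primary outcome it says that "this sample size will detect a 1 point difference on the NODS at 12 months". It closes with: "The proposed hlm analysis will likely have greater statistical power because all observed data are included".

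**The concern.** At Time 0 the arms can differ only by chance. How the model uses that value therefore decides both what is estimated and how precisely.

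- **Main effect.** A Condition main effect over all four times averages one expected zero with three follow-up differences.
- **Change or interaction.** These contrasts remove the dilution. They subtract the whole baseline value, however, although a correlation of .5 supports subtracting only half of it (with equal variances). The surplus is noise.
- **NODS under Hypotheses 2 and 3.** NODS is a primary outcome and baseline NODS is an added factor. If the past-three-month version is meant, the same number is both the Time 0 response and a predictor.
- **Self-rated improvement.** This secondary outcome is listed at follow-up and not in the baseline battery, so a model with Time (0,3,6,12) does not fit it.

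At stake is power that the trial could have from values it already plans to collect, and a clear match between the primary test and the difference on which the trial was sized.

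**Working it through.** **Inputs from the article.** 180 recruited; 15% attrition; about 153 followed; alpha .025 per outcome; power .80; baseline to follow-up correlation .5; about 2 days per month, described as a medium effect.

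**Assumptions.** Medium means d = 0.5 (so an SD of about 2/0.5 = 4 days); two-sided test; 1:1 allocation; 153 followed at every visit (76.5 per arm); a constant difference at 3, 6 and 12 months; equal variances and one correlation ρ between all visits, with a range of .3 to .7.

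**1. The plan's own figure.** n per arm = 2(z₀.₉₈₇₅ + z₀.₈₀)²/d² = 2(2.241 + 0.842)²/0.25 = 76.04, so 77. The total is 154 (stated 153). Dividing by .85 gives 182 (stated 180), and 180 × .85 = 153. At ρ = .5 a change score has SD √(2(1 − .5)) = 1, so a single-visit comparison and a 12-month change score give the same N. A baseline-adjusted comparison has variance 1 − .5² = .75 and would need 58 per arm, 116 in total, 137 after attrition. The stated size therefore takes no credit for adjustment.

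**2. Competing tests.** Power = Φ(δ/(SD × √(2/76.5)) − 2.241), with √(2/76.5) = 0.1617. In SD units at ρ = .5:

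- Condition main effect, four times: δ = (0 + 3 × 0.5)/4 = 0.375; variance (1 + 3ρ)/4 = .625.
- 12 months minus baseline: δ = 0.5; variance 2(1 − ρ) = 1.
- Follow-up average minus baseline: δ = 0.5; variance 1 + (1 + 2ρ)/3 − 2ρ = .667.
- Baseline-adjusted, 12 months: δ = 0.5; variance 1 − ρ² = .75.
- Baseline-adjusted, follow-up average: δ = 0.5; variance (1 + 2ρ)/3 − ρ² = .417.
- Condition x Time, 3 df: noncentrality = (76.5/2) × 0.25 × 0.75/(1 − ρ) = 14.34.

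| Test | ρ = .3 | ρ = .5 | ρ = .7 |
|---|---|---|---|
| Condition main effect, Times 0, 3, 6, 12 | 86.9% | 75.6% | 65.3% |
| 12 months minus baseline | 64.5% | 80.3% | 96.0% |
| Condition x Time, 3 df | 68.0% | 84.8% | 98.2% |
| Follow-up average minus baseline | 83.1% | 93.9% | 99.6% |
| Baseline-adjusted, 12 months | 84.1% | 90.8% | 98.2% |
| Baseline-adjusted, follow-up average | 99.2% | 99.5% | over 99.9% |

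**3. What the table shows.** On the main-effect reading, 2 days becomes 0.75 × 2 = 1.5 days, and 80% power at ρ = .5 would need 170 followed. For the same target, adjustment beats the change score at every ρ shown: at ρ = .5, from 80.3% to 90.8% at 12 months and from 93.9% to 99.5% for the average. Part of the distance from 80% to over 99% comes from averaging three visits rather than from adjustment.

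**4. NODS on both sides.** At Time 0 the predictor equals the response (slope 1, no residual). At follow-up the planning correlation implies a slope of about .5. A single coefficient for baseline NODS cannot describe both.

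**The case against.** The strongest reply is that nothing in the article makes the Condition main effect the test. Listing two factors with their levels does not exclude their interaction. Hypothesis 1 concerns reductions in one arm compared with the other, which is a Condition x Time question. The power section targets follow-up differences, and its N reproduces as a single-visit or change comparison, not as the diluted average, which would need 170 followed. All of this stands. A reader might infer that the primary estimate is biased toward zero by a quarter, but the documents do not support that.

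Three further inferences also fail:

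- **Time 0 in the response as an error.** It is a standard longitudinal analysis. With a common baseline mean it is about as efficient as covariate adjustment.
- **The mixed-model power statement as false.** It is worded as likely. At ρ = .5 the 3-df test (84.8%) and the average change (93.9%) exceed the planned 80%. Only the main-effect reading contradicts it.
- **A collapse in power if the effect builds up over time.** No such trajectory appears in the article, which assumes the 2-day difference at each follow-up.

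A condensed article may also leave the exact contrast and covariance structure to a fuller plan, so the unnamed contrast alone is not a fault. What the reply does not answer is that the article fixes baseline as a response level without stating an adjustment, when a better use of the same values is available. It also leaves the NODS overlap and the missing Time 0 value for self-rated improvement.

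**Conclusion.** The point holds as an improvement in method. For the same follow-up target, baseline adjustment cuts the 12-month variance from 1 to .75 of the single-visit variance and lifts power by about 10 points at the article's own correlation. The planned sample size is not undermined: at r = .5 the change and interaction readings keep at least 80%. The one-quarter shrinkage and 76% power apply only if the main effect were the test, and the article does not say so. Every power figure rests on the assumptions listed in the working, chiefly d = 0.5 and equal correlations, since the article gives no SD. At ρ = .3 the single-visit change and 3-df tests fall below 80%, while both adjusted contrasts stay above it. The NODS and self-rated improvement points do not depend on how the interaction is read, but they concern the moderator analyses and a secondary outcome.

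**What to change.** Reword the Analyses plan as follows:

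- For each primary outcome, take 3, 6 and 12 months as the response, with the baseline value of that outcome as a covariate. Alternatively, keep Time 0 in the response and constrain the arms to a common baseline mean.
- Include Condition, Time and Condition x Time.
- Name one contrast per primary outcome and test it at .025, for example Condition at 12 months or averaged over the follow-ups.
- Use the same form for Hypotheses 2 and 3. When NODS is the outcome, baseline NODS enters once, not as both Time 0 response and predictor.
- Model self-rated improvement on the follow-ups only, without a baseline value of its own.

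The cost is wording. All baseline values needed are already in the planned assessment, and neither sample size nor visits change. The choice should be fixed before outcomes are seen by arm.

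### Read literally, the primary model is a random intercept; if correlations between visits are not constant, the 12-month test of change from baseline could run at about .04 to .05 instead of .025

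*Protocol article*

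**What the plan says.** In the protocol article, Analyses plan, the primary analysis of Hypothesis 1 "will be based on the appropriate random effects model to properly account for the longitudinal nature of this data". The next sentence gives the structure: "Condition (2) and Time (0,3,6,12) will be modeled as fixed factors while the participants will be modeled as random factors". No random slope, residual covariance or robust standard error is named, and none is ruled out. The contrast that decides Hypothesis 1 is not named either.

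Follow-up assessment sets unequal spacing: "After three, six and twelve months, a follow-up assessment of gambling behaviour (timeline method"). With baseline, the gaps are 3, 3 and 6 months.

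Sample size and power analysis works with "a Bonferroni corrected α = .025 (.05/2 outcome variables") and one correlation for all visits, "assuming a correlation of .5 between baseline and follow-up values, power = 0.80". The target is to "detect a difference of about 2 gambling days per month between conditions at each follow-up interval (medium effect size"), plus one NODS point at 12 months. It adds that "these calculations are based upon a more simple repeated measures ANOVA model" and expects the hierarchical model to have more power.

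**The concern.** A random participant term with independent residuals gives every visit the same variance and every pair of visits the same correlation. Three features of this trial make that doubtful.

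- The last gap is twice as long as the others.
- Baseline is a selected, pre-treatment state: entry requires gambling in the past month and a PGSI score of 3 or more. The intervention then falls between baseline and all follow-ups.
- Days and dollars are calculated for each follow-up period, so on the natural reading the 12-month value covers six months and the earlier ones three. This does not extend to NODS, for which no follow-up window is given.

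Baseline is a level of Time, and Hypothesis 1 concerns reductions relative to control. The natural contrast is therefore a difference in change from baseline. If baseline correlates less with 12 months than the average pair of visits does, the random intercept understates the variance of that change and the p-value is too small. A true size of .04 to .05 per outcome would cancel most of the Bonferroni step from .05 to .025.

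**Working it through.** **Inputs from the document.** Visits at 0, 3, 6, 12 months; α = .025 per primary outcome; power .80; correlation .5 between baseline and follow-up; medium effect; 180 randomized, about 153 followed; 15% attrition.

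**Assumptions.** Two-sided test, 1:1 allocation, standardized effect 0.5 for medium, and all correlations between follow-ups.

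**1. The plan's own figure.** SD of change in units of the raw SD = √(2(1 − .5)) = 1. Then n per arm = 2 × (2.2414 + 0.8416)² / 0.5² = 76.04, or 77 with the t correction, so 154 in total. 154 / .85 = 182 against the stated 180, and 180 × .85 = 153 as stated. The sample size is reproduced. Because the SD of change equals the raw SD at r = .5, it does not show whether a difference in change or in level was meant.

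**2. Size of the change test under a random intercept.** With balanced data, mean variance v and mean covariance c:
- model variance of a change ∝ 2(v − c)
- true variance of the 12-month change ∝ σ₀² + σ₁₂² − 2cov(0,12)
- size = 2[1 − Φ(2.2414 / √ratio)], where ratio = true / model.

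With equal variances the ratio is (1 − r₀,₁₂) / (1 − average r). A size of .05 needs a ratio of (2.2414 / 1.96)² = 1.31.

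| Assumed correlations: baseline with 3/6/12; follow-ups 3–6, 3–12, 6–12 | Average r | Ratio at 12 months | Size |
|---|---|---|---|
| all .5 | .500 | .500/.500 = 1.00 | .025 |
| A: .5/.45/.4; .60, .50, .60 | 3.05/6 = .508 | .600/.492 = 1.22 | .042 |
| B: .5/.4/.3; .60, .50, .60 | 2.90/6 = .483 | .700/.517 = 1.35 | .054 |
| C: .5/.5/.5; .70, .65, .70 | 3.55/6 = .592 | .500/.408 = 1.22 | .043 |

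Pattern C keeps the protocol's own .5 with baseline, and its size is the same at every follow-up. Steeper decay by months gives more: .050 when r = .5 at 3 months and keeps decaying, and .082 when it decays to .5 at 12 months. In those cases the 3-month change test is conservative (.007 and .002).

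**3. Simulation.** With 76 per arm and 20,000 runs, the random intercept gave .042 and .054 at 12 months for patterns of types A and B, and .043/.044/.041 at 3/6/12 months for type C. An unstructured covariance gave .022 to .027 throughout. Separately, 1,500 REML random-intercept fits per scenario (N = 180, 15 to 20% dropout) gave .023 with all correlations .5, .039 with .5 to baseline and .7 between follow-ups, and .067 with decay of .7 per 3 months.

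**4. Unequal variances.** Let the SDs at baseline and 12 months be 10% lower (.9, 1, 1, .9). For pattern A, v = (.81 + 1 + 1 + .81)/4 = .905 and c = (.45 + .405 + .324 + .60 + .45 + .54)/6 = .4615. The ratio is (1.62 − .648) / (2 × .4435) = .972/.887 = 1.096, and the size is .032. Pattern B falls to .042. At 15% lower, A and B fall to .027 and .036.

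**5. Other contrasts.** For a 12-month difference in level the ratio is σ₁₂²/v, which is 1 under equal variances, so the size is .025 whatever the correlations (simulated .023 to .030). With SDs rising .8/.9/1.0/1.1 it is 1.21/.915 = 1.32, size .051. The omnibus Condition by Time test lies between .025 and .043 over the equal-variance patterns tried.

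**The case against.** The strongest reply is that the text does not commit to a random intercept only. It asks for an appropriate random effects model, then sorts factors into fixed and random. Power is calculated from a simpler ANOVA that is expressly not the analysis model. Residual covariance is ordinary SAP content, and a condensed article need not give it. This stands in part: slopes and residual structure are left open. But the sentence that specifies the model names participant alone as random, and a SAP that followed it literally would inherit the problem. The remedy is also a more robust method than the one stated, not only a request for detail.

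The second reply is that the size comes from chosen inputs. This stands. The document gives one correlation, .5, and held constant that produces no error. Selection at baseline and averaging over a longer window could lower the variances at 0 and 12 months, which reduces the inflation, as shown above.

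The third is that the plan may intend a comparison of levels, since the power section speaks of differences between conditions at each follow-up. Under equal variances that comparison keeps its .025.

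A reader might infer that the primary standard errors and p-values are wrong, or that any 12-month arm comparison has twice its nominal error. The document supports neither. The contrast is not named, the correlations are not given, and only one of the three main patterns (B) goes past .05.

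**Conclusion.** The point holds conditionally. If the model is fitted as literally written, the test is of change from baseline, and correlations depart from constancy in the expected direction, then the 12-month size is about .04 to .05 instead of .025. The full range over the patterns tried with equal variances runs from .025 to about .08. These figures assume a two-sided test, 1:1 allocation and, except where stated, equal variances; where dropout was simulated it was completely at random. This is a cheap and worthwhile improvement to the primary analysis, not a demonstrated error in it.

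**What to change.** Amend the Analyses plan to state that the four repeated measures (0, 3, 6, 12 months) are modelled with an unstructured covariance, or that the random intercept is kept with robust (sandwich) standard errors. Name the Condition by Time contrast that tests Hypothesis 1, and apply the same choice to every primary and secondary outcome that has a baseline value.

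The unstructured form is preferable where data are incomplete, because sandwich errors repair the standard errors but leave the working covariance misspecified. It needs 4 variances + 6 covariances = 10 parameters, which 180 participants can support. The cost is one or two sentences, a few more covariance parameters, and a prespecified simpler structure if the model does not converge. No extra data are needed.
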